#### Sample size calculation

2.10.1.

The sample size calculation has been based on the most relevant clinical efficacy outcome measure, which is the proportion of patients with at least one recurrence of infection at 24 months.

Available data show rates of 4 to 5% when using Cerament-G, for durations between 5 and 21 months (10, 11); as the follow-up is longer in the CONVICTION study (24 months), the hypothesis chosen was a rate of 6%. On the other hand, the proportion of recurrence of infection in the standard of care is estimated at 20% (21). The total number of patients to be randomized in the study will be 200 (100 per group; considering alpha-risk at 0.05, power of 80% in a bilateral situation and approximately 10% of early withdrawal).

The estimate of the number of subjects needed according to medico-economic hypothesis would require numerous hypothesis, leading to uncertainty. Only the cost of Cerament-G and hospitalizations for recurrence of infection, and the impact on the short-term utility of the surgery for recurrence of infection (6% in the innovative strategy vs. 20% in the standard of care), fractures and amputations (5% in both groups) have been taken into account. We hypothesize that the utility is decreased 6 months before revision surgery, 3 months after revision surgery, 9 months after amputation and 3 months after fracture. As no utility data are available in the literature for “before surgery” and “after surgery” conditions, they have been estimated according to expert opinion. As little data is available in the literature for health states comparable to the health states “after fracture” and “after amputation” and for the sake of homogeneity of the measurement, the utility concerning these states has also been estimated by expert opinion. However, these data seem consistent with the closest data available (22).

The utility scores used to value these health conditions are as follows:

- Before surgery = 0.8- After surgery = 0.49- After fracture = 0.28- After amputation = 0.39

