Regarding costs, the average cost per patient only for Cerament-G and for the innovative strategy group was estimated at 2,664 € (based on the assumption of using 15 ml of product for a third of patients and 10 ml for the remaining two-thirds). The average cost of a hospital stay was estimated, according to the French study on cost taking into account the different levels of severity, at €13,776 for a leg amputation and at €3,330 for a broken leg. Finally, the cost of a recurrence of infection was estimated, according to an expert, at approximatively €10,000.

The average cost difference hypothesis was €1,144, with a standard deviation at €1,000, and the average difference of QALY hypothesis was 0.04, with a standard deviation at 0.03. For a maximum willingness to pay of €50,000, a correlation coefficient of −0.03, an alpha risk of 5% and a beta risk of 20%, with 10% of early withdrawal, the number of subjects needed was estimated at 196 (98 per group). As this estimate is conservative, the estimated number of subjects needed corresponds to a high value.

The randomization of 200 patients in the study will therefore validate both the efficiency and the clinical efficacy hypotheses. Finally, considering that 10% of patients whose inclusion will be invalidated by the Patient Eligibility Validation Committee, a total of 220 patients will be included.

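### The SDs behind the economic sample size (€1,000 and 0.03 QALY) cannot hold under the plan's own event model, so power for the primary cost-utility outcome is about 10%, not 80%

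*Protocol article*

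**What the plan says.** The primary outcome (section 2.5) is the incremental cost-utility ratio at 24 months. Section 2.10.1 first sizes the trial on recurrence of infection and then gives a second calculation for the economic hypothesis. Its inputs are stated as follows: "The average cost difference hypothesis was €1,144, with a standard deviation at €1,000, and the average difference of QALY hypothesis was 0.04". The QALY SD is set at 0.03. It continues: "For a maximum willingness to pay of €50,000, a correlation coefficient of −0.03", with alpha 5%, beta 20% and 10% withdrawal, and arrives at 196 patients (98 per group).

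The same section gives the model behind the means. Recurrence is "6% in the innovative strategy vs. 20% in the standard of care", and "the cost of a recurrence of infection was estimated, according to an expert, at approximatively €10,000". The device costs €2,664 per patient, an amputation €13,776 and a fracture €3,330. Amputation and fracture are each set at 5% in both groups, and expert utilities are listed for four health states. No derivation is given for either SD or for the correlation.

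The section then draws two conclusions: "As this estimate is conservative, the estimated number of subjects needed corresponds to a high value", and "The randomization of 200 patients in the study will therefore validate both the efficiency and the clinical efficacy hypotheses".

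**The concern.** The means and the SDs describe the same patients, so they must come from compatible distributions. A cost that is zero for most patients and €10,000 for a minority has a large SD, which the event rate determines. An SD of €1,000 is too small for that distribution in either group. The QALY SD has the same problem once the stated gain is attributed to avoided recurrences. Because one event raises cost and lowers utility together, the correlation should be strongly negative, and a negative correlation increases the variance of net benefit. All three inputs therefore err in the favourable direction, while the text says the opposite.

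The claim concerns the primary outcome of a trial meant to inform reimbursement. If the device works exactly as hypothesized, the interval for net benefit will still probably include zero. A reader told that the trial had 80% power could take that as evidence against efficiency.

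**Working it through.** **1. The plan's own calculation.** The target incremental net benefit is 50,000 × 0.04 − 1,144 = €856. The patient-level SD of net benefit is √(SDc² + (W·SDq)² − 2ρ·W·SDc·SDq), with W = 50,000.

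- With ρ = −0.03: √(1,000² + 1,500² + 2 × 0.03 × 1,000 × 1,500) = €1,828. Two-sided 5% and 80% power need 72 per group, or 80 after 10% withdrawal (160 in total). The stated 98 (196) is not reproduced.
- With ρ = −0.3 the SD is €2,037 and the need is 89 per group, or 98 to 99 after withdrawal. The printed −0.03 may be a misprint. An unrounded QALY gain near 0.0383 would also give 98 to 99. In each case €1,000 and 0.03 enter as patient-level SDs, not as standard errors.

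**2. The mean cost difference comes from the event model.** 2,664 − 0.14 × (10,000 + 0.05 × (13,776 + 3,330)) = 2,664 − 0.14 × 10,855.3 = €1,144. The match requires reading the 5% amputation and fracture rates as applying to recurrences.

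**3. Cost SD from recurrence alone**, 10,000 × √(p(1 − p)):

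- Standard of care: 10,000 × √(0.20 × 0.80) = €4,000.
- Innovative strategy: 10,000 × √(0.06 × 0.94) = €2,375.

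This step uses only stated figures. Adding amputation and fracture as in step 2 gives €4,557 and €2,687.

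**4. QALY SD from the stated gain.** Loss per recurrence is 0.04 / 0.14 = 0.286. The SDs are 0.286 × 0.400 = 0.114 and 0.286 × 0.2375 = 0.068.

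**5. QALY SD from the stated utilities.** An event-free utility is needed and none is given; 1.0 is assumed.

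- Recurrence: 0.5 × (1 − 0.80) + 0.25 × (1 − 0.49) = 0.2275.
- Amputation: 0.75 × (1 − 0.39) = 0.4575.
- Fracture: 0.25 × (1 − 0.28) = 0.18.
- Mean gain: 0.14 × (0.2275 + 0.05 × 0.6375) = 0.0363, which rounds to 0.04. A baseline of 0.95 gives 0.0307.
- SDs: 0.114 and 0.067, with a cost-QALY correlation of about −0.99.

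**6. Power with 90 evaluable per group.** The full model gives net-benefit SDs of €10,248 and €6,023, against €1,828 implied by the printed inputs. The SE is √((10,248² + 6,023²)/90) = €1,253, and the 95% half-width is 1.96 × 1,253 ≈ €2,460. Power at €856 is Φ(856/1,253 − 1.96) plus the small lower tail = 10.5%. At the unrounded net benefit of 50,000 × 0.0363 − 1,144 ≈ €671 it is 8.3%.

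**7. Sensitivity, all at €856 and 90 per group:**

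| Assumption | Power |
|---|---|
| Printed SDs, ρ = −0.03 | 88% |
| Printed SDs, ρ = −0.3 | 80% |
| Recurrence cost only, QALY variance zero | 42% |
| Only cost SD corrected (pooled €3,289) | 35% |
| Only QALY SD corrected (pooled 0.094) | 22% |
| Both SDs corrected, ρ = −0.03 kept | about 16–17% |
| Recurrence only, utilities with baseline 1.0 | 12.9% |
| Full model, baseline 0.80 | 17% |
| Full model, baseline 0.90 | 12.8% |
| Full model, baseline 1.0 | 10.5% |
| Amputation and fracture in 5% of all patients, baseline 1.0 | 8% |

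80% power in the full model needs about 1,510 evaluable per group at baseline 1.0 and about 710 at baseline 0.80.

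**The case against.** Five points can be made for the plan.

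- **Only the cost SD is contradicted by stated rates and costs alone.** This is correct. The utilities need a baseline that the article does not give, and at 0.80 the QALY SDs fall to 0.051 and 0.030. However, that baseline yields a gain of only about 0.014 QALY. Only a baseline close to 1.0 is compatible with the stated 0.04, and step 4 reaches the same SDs from that gain without using a baseline.
- **The figures of 10% and 1,500 per group are model-dependent.** This stands, and ranges are given above. None approaches 80%.
- **The printed correlation may be a misprint for −0.3.** This is plausible, since it reproduces 98 per group. It does not rescue the SDs: with both corrected, power at ρ = −0.3 is about 14%. The value −0.99 belongs to the plan's simplified model and does not predict what the trial will observe.
- **The sample size rests on recurrence, and the section warns that the economic estimate is uncertain.** Both are true, and the recurrence calculation reproduces (90 per group, 100 with withdrawal). But the section then resolves the uncertainty the wrong way by presenting 196 as a high value.
- **The plan does not test net benefit against zero.** Sections 2.7.4 and 2.10.2 describe a cost-utility plane, an acceptability curve and a confidence interval for the ratio. That makes the misreading a risk rather than a certainty. It also makes a power claim harder to justify, because the planned analysis is already one of estimation.

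**Conclusion.** The concern holds. The cost SD of €1,000 is incompatible with the stated recurrence rates and cost in both groups, and the QALY SD of 0.03 is incompatible with the stated gain of 0.04. Power for the economic hypothesis is about 10% under the plan's own model, taking an event-free utility of 1.0, amputation and fracture at 5% of recurrences, a two-sided 5% test and 90 evaluable per group. Varying the baseline, the correlation and the amputation reading gives 8% to 17%. Ignoring QALY variation altogether gives 42%. Ordinary variation in EQ-5D scores and in other resource use, which the model leaves out, would lower power further. The statements that the estimate is conservative and that 200 patients validate the efficiency hypothesis are therefore wrong and must be corrected. The recurrence sample size is not affected.

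**What to change.** In section 2.10.1, and in the SAP if it repeats the calculation:

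- Delete the statements that the economic estimate is conservative and that 200 patients will validate the efficiency hypothesis.
- State that 200 is justified by the recurrence outcome only and that the cost-utility analysis is one of estimation.
- Recompute the cost SD, QALY SD and correlation from the stated rates, costs and utilities. State the event-free utility and whether the 5% amputation and fracture rates apply to all patients or to recurrences. Correct or confirm the printed correlation, since the printed inputs give 160 patients rather than 196.
- Report the expected precision of incremental net benefit with its assumption. From event variation alone, with the 5% rates applied to recurrences, the 95% half-width is about ±€2,500 at an event-free utility of 1.0, ±€2,065 at 0.90 and ±€1,677 at 0.80.

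The cost is wording and a short recalculation. Recruitment, design, endpoint and analysis are unchanged. The price is that a stated 80% power for the primary outcome gives way to a much less favourable figure.

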#### Statistical analysis

2.10.2.

The characteristics of the overall population and the two groups will be described. The analysis will be carried out on an intention-to-treat basis. Usual descriptive statistics will be presented for costs and QALYs. Depending on normality test results, mean costs will be compared across groups using Student’s t-test or non-parametric bootstrap. The 95% confidence interval for incremental cost-utility ratio will be computed using Fieller’s method or the bootstrap method. Deterministic sensitivity analyses will be performed, the results of which will be presented in a tornado diagram.

The statistical analysis to estimate the treatment effect on clinical outcomes will be based on the following methods: a linear regression model adjusted for stratification criteria for continuous variables; a logistic regression model adjusted for stratification criteria for dichotomous variables; and a Cox model adjusted for stratification criteria for survival data.

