### Randomization

2.3.

Patients will be randomized between the two strategies in a balanced manner with a computerized and secure system *via* the internet. Randomization will be carried out by minimization, using a computer algorithm that calculates in real time the allocation of the group that guarantees the best possible balance, taking into account the patient’s stratification values (center and preventive stabilization) as well as the patients already randomized. So that the randomization is not predictable, a part of randomness will be added to the algorithm.

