### Primary outcome measure

2.5.

The primary outcome is the incremental cost-utility ratio estimated at 24 months between two treatments strategies for chronic long bone osteomyelitis.

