#### Economic secondary outcome measures

2.6.2.

- Cost of both strategies estimated at 24 months;- Cost of a corticotomy procedure using Cerament-G;- Estimated utility based on the Euroqol EQ-5D questionnaire and on utility scores validated on the French population at inclusion, at S + 4/S + 6, M3, M6, M12, M18 and M24 (usual follow-up visits) as well as after each repeat surgery according to the same schedule;- Incremental cost-effectiveness ratio estimated at 24 months with no recurrence of infection as efficacy outcome measure;- Budget impact analysis carried out from the perspective of the French Health Insurance.

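### The article names only unadjusted methods for the primary cost-utility contrast and no use of inclusion EQ-5D as a covariate, while clinical outcomes are adjusted for the stratification criteria

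*Protocol article*

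**What the plan says.** Section 2.5 sets the target: "The primary outcome is the incremental cost-utility ratio estimated at 24 months". Section 2.10.2 then gives its analysis in three steps:

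- "Usual descriptive statistics will be presented for costs and QALYs".
- For costs, with the choice made by a normality test: "mean costs will be compared across groups using Student’s t-test or non-parametric bootstrap".
- For the ratio: "The 95% confidence interval for incremental cost-utility ratio will be computed using Fieller’s method or the bootstrap method".

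None of these names a covariate. The next paragraph of the same section, limited to clinical outcomes, does: "a linear regression model adjusted for stratification criteria for continuous variables", with logistic and Cox models adjusted in the same way.

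Section 2.3 allocates patients by minimisation on centre and preventive stabilisation. Section 2.6.2 and Table 1 show that EQ-5D is measured before surgery, with "utility scores validated on the French population at inclusion" and at each later visit. Section 2.4.2 places randomisation after the eligibility committee has validated the inclusion. The article does not say that the inclusion EQ-5D will serve as a covariate.

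**The concern.** Secondary clinical outcomes receive adjustment for the minimisation factors, and the primary outcome, as described, does not. Two things are at stake.

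First, precision. Minimisation removes between-arm differences in centre and stabilisation. An analysis that leaves those factors out still counts their variation as noise, so its intervals tend to be wider than necessary to the extent that the factors predict cost or utility.

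Second, conditional bias in the QALY difference. Minimisation does not balance baseline utility. If patients who start with better utility tend to keep it, any chance difference at inclusion is carried into the 24-month QALY difference. The planned effect is small enough for this to matter.

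**Working it through.** **Inputs from the article (sections 2.10.1 and 2.7.1).** Cost difference €1,144; QALY difference 0.04 with SD 0.03; willingness to pay €50,000 per QALY; 100 per group randomised; horizon 24 months.

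**Reproducing the planned effects.**

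- Cost: 2,664 − 0.14 × 10,000 − 0.14 × 0.05 × (13,776 + 3,330) = €1,144, reading the 5% fractures and amputations as applying to recurrences.
- QALY: the loss per recurrence, measured from a utility of 1, is 0.5 × 0.20 + 0.25 × 0.51 = 0.2275. Fractures and amputations add 0.05 × (0.25 × 0.72 + 0.75 × 0.61) = 0.0319. The difference is 0.14 × (0.2275 + 0.0319) = 0.036, which rounds to 0.04.

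**Planned net benefit.** 50,000 × 0.04 − 1,144 = €856. In QALYs this is 856 / 50,000 = 0.0171. Spread over two years it is a utility difference of 0.0086 (discounting ignored).

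**Size of a chance imbalance.** The article gives neither the SD of baseline EQ-5D (s) nor the QALYs gained over 24 months per unit of baseline utility (b). Both are assumptions here: s from 0.15 to 0.30, and b from 0.5 (a quarter of a baseline difference persists on average) to 2 (all of it persists). With 100 per group:

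- one-SE imbalance = s × √(2/100)
- shift in net benefit = 50,000 × b × imbalance

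Each cell shows the one-SE shift and, in brackets, the probability that the absolute shift exceeds €856.

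| s | b = 0.5 | b = 1 | b = 2 |
|---|---|---|---|
| 0.15 | €530 (11%) | €1,061 (42%) | €2,121 (69%) |
| 0.20 | €707 (23%) | €1,414 (54%) | €2,828 (76%) |
| 0.25 | €884 (33%) | €1,768 (63%) | €3,536 (81%) |
| 0.30 | €1,061 (42%) | €2,121 (69%) | €4,243 (84%) |

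**Check against the plan's own QALY SD.** If the total SD really is 0.03, then b × s cannot exceed 0.03. The one-SE shift is then at most 50,000 × 0.03 × √(2/100) = €212, and 1.96 SE is €416, both below €856. Every cell above needs a larger QALY SD than that (b × s is at least 0.5 × 0.15 = 0.075).

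The 0.03 is itself hard to reconcile with the article's event assumptions. Recurrence alone gives 0.2275 × √(0.20 × 0.80) = 0.091 in the control arm and 0.2275 × √(0.06 × 0.94) = 0.054 in the Cerament-G arm, before any other spread between patients. The planning SD therefore neither confirms nor rules out the table.

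**Direct weight of the baseline value.** The article gives no rule for building QALYs. If trapezoids were used from inclusion to about week 5, the baseline value would carry 2.5/52 = 0.048 QALY per unit. An imbalance of 0.021 to 0.042 would then move net benefit by only €51 to €102. Nearly all of the shift in the table comes from persistence.

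**The case against.** The case for leaving the plan alone has several sound parts.

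- **The article is a summary.** An analysis plan that is not shown may specify adjusted QALYs, and both Fieller and bootstrap intervals can be built on adjusted estimates. This stands. The text does not exclude adjustment. It names unadjusted methods for the primary contrast beside adjusted ones for the secondary outcomes, and that contrast is what needs settling.
- **Randomisation makes the unadjusted contrast unbiased.** Its intervals already allow for chance imbalance, and omitting minimisation factors tends to make them conservative. This also stands. A reader might infer that the primary analysis is invalid; it is not. What remains is lost precision and bias conditional on the imbalance that happens to occur.
- **QALYs are analysed.** Read alone, the sentence on descriptive statistics might suggest that no inference on QALYs is planned. An interval for the ratio requires inference on the QALY difference, and section 2.7.4 provides for an acceptability curve if the strategy proves more costly and more effective.
- **The size is assumed.** Correct, and with the planning SD of 0.03 the shift would be unimportant.
- **Adjustment will not rescue power.** Take s = 0.25, b = 1 and an assumed baseline-to-QALY correlation of 0.5. The QALY SD is then 1 × 0.25 / 0.5 = 0.5. At 90 per group the SE falls from 0.5 × √(2/90) = 0.0745 QALY (€3,727) to 0.0745 × √(1 − 0.25) = 0.0645 (€3,227), still far above €856. Adjustment improves the estimate but does not repair the planning variance, which is a separate matter.
- **The normality test does little harm.** Both branches target the mean, and skewed costs would usually lead to the bootstrap anyway.

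**Conclusion.** The point holds as a prespecification improvement at no data cost, not as an error that invalidates the trial. The article states no adjustment for its primary contrast, although it adjusts the clinical outcomes, minimises on two known factors and collects baseline utility.

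The firm figure is the smallness of the planned effect: €856, or about 0.0086 of utility over two years. The shift of about €530 to €4,240 for a one-SE imbalance is illustrative and rests on an assumed baseline SD and persistence. It may be tempting to conclude that chance imbalance will outweigh the treatment effect. The article does not support that, since two of the twelve assumed combinations give a one-SE shift below €856 and the planning SD of 0.03 would put it no higher than €212. It supports only that the result could be sensitive to baseline utility and that a simple safeguard is available.

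**What to change.** State in the analysis plan, before any comparison by arm, that:

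- incremental costs and QALYs are estimated jointly by regression, for example seemingly unrelated regression, on arm, preventive stabilisation and centre, with the pre-randomisation EQ-5D added to the QALY equation;
- centre enters as a random effect or with small centres pooled, since 200 patients are spread over the 14 reference centres of the abstract or the 12 university hospitals of section 2.1;
- intervals for the adjusted incremental cost, incremental QALY, and ratio or net benefit come from a bootstrap that resamples patients within arm, keeps each patient's cost and QALY together, and refits both equations;
- the unadjusted comparison is reported as a sensitivity analysis.

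Always using the bootstrap for mean costs, in place of the normality test, is a minor simplification that can be made at the same time.

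The cost is a few sentences of wording, as every variable is already collected. Fixing it in advance matters because adjustment chosen after an imbalance has been seen would be open to challenge in the reimbursement decision the trial is meant to inform.

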## Discussion

3.

Despite the progress made in both antibiotics and surgical treatment, the management of chronic osteomyelitis of long bone could be improved. Probability of failure of treatment is around 20% and that rate has unfortunately remained stable for more than 20 years. As it is mainly a local disease, the only way to improve the prognosis is probably to act locally, to increase the probability of pathogen eradication, and to prevent superinfection and fracture.

One historical way to better target the pathogen responsible for infection is to deliver conventional local antibiotics during surgery, but all traditional antibiotics usable for injections are available in liquid form after reconstitution. Some surgeons historically performed bone washing with rifampin or with gentamicin. However, during surgical intramedullar debridement, bone bleeding mechanically pushed away liquid antibiotics that could be used intramedullary. Moreover, the half-life of conventional antibiotics usable intravenously is very short, with no residual active drug 24 h after their reconstitution.

Some authors discussed performance of autologous bone graft to fill the dead space, or the use of antibiotic-impregnated PMMA cement (beads or cementoplasty). However, biomechanically, the bone does not need bone graft in stage III long bone osteomyelitis. Unlike Cerament-G, PMMA cement is not resorbable. Subsequent surgery is required to remove it, and once it is removed, a dead space still remains and must be managed; a biomechanically unnecessary bone graft is often placed at the time of PMMA explantation. Significant complications and morbidity could be associated with this strategy which is recognized as controversial and non-optimal. Finally the Papineau technique is the performance of bone debridement with keeping the wound open and the bone exposed, with performance of serial bone grafting before performing of a skin graft is clearly no longer proposed in contemporary times. Of note, none of these techniques are considered as the standard of care procedure for dead space management, and these practices seem to be largely heterogeneous. In certain situations, surgeons do not have access to Cerament-G or other bone substitutes. Since the superiority of using such devices has not yet been demonstrated, leaving the dead space empty is a current option for stage III long bone osteomyelitis.

Emergent potential local anti-infective treatment, phage or phage-derived therapies could also be future options. Bacteriophages are natural viruses that target specifically a bacterial species. They have the ability to replicate themselves in their host, and can be deliver locally. This lysin, can destroy the bacteria; it also has anti-biofilm properties (23). Phage therapy is a potentially innovative approach for patients with bone and joint infection, but there are major drawbacks: (i) few phages are available at this time, targeting only few bacteria such as *S. aureus* or *P. aeruginosa*; (ii) it is necessary to identify the pathogen(s) responsible for the infection before the surgery, to select active phages after determining phage susceptibility. This is not feasible in patients with chronic osteomyelitis. Phage-derived therapies such as the use of lysins, which are biologically active enzymes, could be of interest for the future (24), as an antibiotic-nanoencapsulated in gel that could be used locally (25).

Finally, the use of a resorbable synthetic bone substitute with local antibiotic eluting capability, such as Cerament-G, having a wide spectrum of activity against the most frequent bacteria involved in the disease, could be the most relevant way to improve the prognosis of chronic osteomyelitis. Indeed, firstly, a bone substitute that has the ability to fill the “dead space” that is caused during surgery, will prevent the stagnation of blood in the intramedullar space. This phenomenon of bone void is a favorable environment for the persistence of the initial pathogen and is probably a factor which promotes the risk of superinfection due to another pathogen that can contaminate the intramedullar cavity during surgery. Secondly, the local delivery of high doses of gentamicin (that is a broad-spectrum bactericidal antibiotic effective against the vast majority of bacteria involved in osteoarticular infections) at prolonged concentrations for several weeks is also a great advantage to treat the current infection (in combination with systemic antibiotics) and prevent superinfection. Finally, a resorbable bone substitute promotes the regeneration of the bone within this space, limiting in theory the risk of fracture during follow-up.

Two prospective studies have shown that Cerament-G was associated with a low number of infectious recurrences (about 5%). However comparative studies, directly evaluating the effectiveness and efficiency of this medical device, are lacking. The CONVICTION study proposes a protocol for a clinical and economic evaluation of an innovative device that could, despite an additional initial cost, lead to fewer costs in the future, while improving the utility of patients. Its results will allow to identify whether the use of Cerament-G during surgery is a cost-effective alternative strategy, compared to the absence of filling the dead space during surgery. This control group strategy was chosen as there is currently no consensus on the management of the patients concerned, and as it seems to represent the current majority practice in France. Furthermore, the randomized design of the study will provide relevant results on the clinical benefit of using such a resorbable synthetic bone substitute with local antibiotic eluting capability for osteomyelitis management.

Study findings could also have an impact on the decision of the funding of this expensive device by French health insurance. To our knowledge, there are no other medico-economic studies published or in progress on this topic.

Osteoarticular infections, including chronic osteomyelitis, represent such a high cost that the cost of even a preventive medical device can be offset by the costs of the infections that the device could prevent (26). More generally, we therefore hope that the results of this study will help to show the clinical and economic impact that a device for preventing osteoarticular infections can have.

The study is done throughout the network of CRIOAc in France, in referral centers for the management of complex infections. This network was established in 2009, and its aim is to treat all French patients by offering specialized medical advice at our centers, located across the country. It would be a key process to perform clinical trials in teams dedicated to the management of bone and joint infections, with experience and skills that have grown since the establishment of these centers (27). Of note, recent epidemiological data show that there is a significant number of long-bone osteomyelitis managed in the network, which leads us to believe that the study is feasible in France (28).

This study has several limitations and particular biases. First, the complete adherence of the investigators is needed, especially if we focus on the training of the surgeons who manipulate the device, and only patients without post-debridement dead space management can be included. Secondly, it was impossible to blind the surgeon, who knows at the time of surgery, if the patient will receive or not the Cerament-G. It is of importance that the surgical debridement of the osteomyelitis of a particular patient has to be the same whether the patient is randomized to one arm or another. Finally, we decided, in particular to collect the data needed to estimate the informal care costs, to use a patient notebook to collect healthcare consumption. This mode of collection can lead to biases if the documents are not correctly completed. However, we closely monitor the filling of the patient notebooks and, if this is not satisfactory, we will consider linking the trial data with the National Health Data System (NHDS) in order to estimate the costs.

